### Trial management and monitoring

#### Trial monitoring

The TASC standard operating procedure (SOP) on adverse event (AE) recording will be adhered to for reporting of harms in this study.

This study is low risk and no adverse events are expected from this one-off intervention, which consists of a standard dental procedure (extraction of a tooth). The proposed intervention is less invasive than the standard procedure (and actually forms a part of it). Both the standard procedure and, therefore, the proposed intervention are considered unlikely to result in serious adverse events (SAEs) or suspected unexpected serious adverse reactions (SuSARS). Any participants reporting AEs would discuss this with clinic staff or may contact the trial team directly. All relevant AEs and SAEs will be recorded from the time a participant consents to join the study until day 10 post-initial treatment.

Hospital admissions, changes in concomitant medications, or other health problems will not be reported as AEs or SAEs unless there is direct evidence that the AE has been caused by the intervention. However, should they occur, they will be recorded in keeping with normal practice.

While it is anticipated that the incidents of SAEs and reactions to the treatments will be rare, there are a number of common, and well-understood consequences of the use of dental anesthetics (local anesthetic (LA), inhalation sedation (IHS), general anesthetic (GA), sedation) and extractions. A listing of the common and well-understood consequences of treatment, less common side effects, and rare events can be found in Table 2.

**Table 2 T2:** Common and well-understood consequences of treatment

**Intervention**	**Adverse events**		
	**Common and well-understood consequences of treatment**	**Less common and unpleasant side-effects**	**Rare events**
**Extraction of tooth**	• pain around site	• early and delayed post extraction bleeding	• temporo-mandibular joint pain
	• swelling	• infection of socket	• fracture of mandible
	• loss of space for developing dentition	• fracture of tooth and surgical procedure to remove remaining portion	• oral-antral communication
**Fillings in teeth and crowns on teeth**	• occlusal discomfort	• pain, pulpitis	• trauma to soft tissues
		• localized reaction to bonding agents or filling materials	
	• damage to adjacent teeth	• dental abscess	
	• caries progression	• facial swelling	
**Local anesthetic injections**	• pain at site of injection (during or immediately following injection)	• self-inflicted trauma to soft tissues	• trismus
			• prolonged altered sensation
			• swelling
			• hematoma
			• allergic reaction
**Inhalation sedation**	• dizziness	• nausea	• loss of consciousness
		• headache	
**General anesthesia**	•nausea and vomiting	• reaction to anesthetic agent	• death
	• drowsiness	• sore throat or nose bleed (depending on type of intubation)	
	• shivering and feeling cold		

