### Blinding

Due to the nature of the proposed intervention it is not possible to blind staff, the children or their carers to the group once it has been allocated.

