#### Trial management and oversight arrangements

The cosponsors of this trial are the University of Dundee and NHS Tayside.

The trial will be coordinated by the Trial Management Group, (TMG) consisting of the chief investigators, investigators, representative(s) of site PIs, TCTU senior clinical trial manager and a statistician. This group will meet regularly throughout the trial.

A TCTU trial manager will oversee and coordinate the study and will be accountable to the chief investigator. The PI at each site will be responsible for checking the CRFs for completeness, plausibility and consistency. Any queries will be resolved by the investigator or delegated member of the trial team.

A delegation log will be prepared for each site, detailing the responsibilities of each member of staff working on the trial.

The Central Trials Office, TCTU, will provide support to the study team. The office will be responsible for randomization, collection of data in collaboration with the trial manager, data processing and analysis. Publication and dissemination of the study results will be coordinated by the chief investigators and the TCTU, who have had an advisory role in this trial.

A Trial Steering Committee has been established to oversee the conduct and progress of the trial. This comprises: the co-chief investigators, co-investigators, a representative from Tayside Medical Sciences Centre, a practitioner representative and a patient representative.

An independent Data Monitoring Committee will not be necessary for this trial as the study is low risk.

Principal investigators and institutions involved in the study will permit trial-related monitoring, audits, Research Ethics Committee (REC) review, and regulatory inspection(s). In the event of an audit, the investigator agrees to allow the sponsor, representatives of the sponsor or regulatory authorities direct access to all study records and source documentation.

This study has been reviewed by the University of Dundee sponsorship review and is considered low risk, however to ensure the study is run to GCP standards the site will be regularly monitored by the Co-Chief Investigator, [name], or a representative of TASC as agreed by the sponsor.

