#### Emergency code-breaking procedure

Emergency code-breaking in this randomized control trial is not applicable because the pattern of tooth extraction is visible.

The proposed intervention is unlikely to result in SAEs or SuSARS. We do not expect to report hospital admissions, changes in concomitant medications or other health problems as AEs or SAEs unless there is direct evidence that the AE has been caused by the intervention. However, should they occur, they will be recorded in keeping with normal practice.

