#### Consent and assent

Where patients attend their own primary care dentist, these dentists will act as principal investigators and will obtain consent from the patients. Patients attending the Dundee Dental Hospital and receiving treatment there will give consent to one of the trial team wherever possible. If this is not possible, a suitably trained dentist will obtain consent. Regardless of location, consent of the patients will be performed by dentists who will be conversant with the study design and protocol, and be GCP trained in line with the Research Governance Framework (RGF).

The parent(s)/legal guardian(s) of all children in the study will provide written informed consent before any study procedures are carried out and a participant information sheet will be provided to facilitate this process. Where possible, and with the agreement of the parent(s)/legal guardian(s), participating children will also be asked to provide written or oral assent. Those not competent in English will be invited to bring an interpreter with them to the subsequent treatment appointment or to request an NHS interpreter, where this service is available.

As part of the consent process parent(s)/legal guardian(s) must agree to researchers and regulatory representatives having access to their medical records for monitoring and audit purposes. Parent(s)/legal guardian(s) may withdraw their consent to participate at any time during the study.

The investigator or delegated member of the trial team and the child should sign and date the Assent form whereas the parent and investigator should sign the Informed Consent form(s) to confirm that consent has been obtained. The participant should then receive a copy of this document and a copy should be filed in the investigator site file (ISF).

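### Hospital admissions, medication changes and other health problems count as adverse events only on direct evidence of causation, so acute events of uncertain cause can be left out of the trial's harm data

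*Protocol article*

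**What the plan says.** Under Trial monitoring, the protocol article first hands harm reporting to a standard operating procedure: "The TASC standard operating procedure (SOP) on adverse event (AE) recording will be adhered to for reporting of harms in this study". It then sets a collection window: "All relevant AEs and SAEs will be recorded from the time a participant consents to join the study until day 10 post-initial treatment".

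The next paragraph restricts what counts. Hospital admissions, changes in concomitant medication and other health problems "will not be reported as AEs or SAEs unless there is direct evidence that the AE has been caused by the intervention". Events that fail this condition get one further sentence: "However, should they occur, they will be recorded in keeping with normal practice".

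The section Emergency code-breaking procedure returns to the rule in softer form: "We do not expect to report hospital admissions, changes in concomitant medications or other health problems as AEs or SAEs", with the same causation exception and the same fallback to normal practice.

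On who knows the allocation, the Blinding section says "it is not possible to blind staff, the children or their carers to the group once it has been allocated". On oversight, Trial management and oversight arrangements says "An independent Data Monitoring Committee will not be necessary for this trial as the study is low risk".

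**The concern.** Whether an event happened and whether the treatment caused it are separate questions, and safety data normally hold both answers. Here the second decides whether the first enters the AE data. An event judged not to meet the threshold leaves no entry there, so the judgment cannot be reviewed from those data.

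The threshold is also high. Direct evidence of causation asks for more than a reasonable possibility. In the first days after an extraction or a general anesthetic the cause of an event is often unclear: an admission for fever or vomiting, or a new antibiotic, may or may not come from the procedure. Hospital admission, a marker of seriousness, is among the event types named.

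What is at stake is how complete the acute harm record is in a trial of children aged 7 to 11 whose results are meant to inform national guidelines. The Introduction says that the additional extraction may shift the choice toward general anesthesia, so acute harm could plausibly differ between the arms.

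**Working it through.** No arithmetic applies. The article states no AE rate, reporting rate or attribution rate, so there is no figure to reproduce and none that would measure this rule's effect. The check is a comparison of the passages.

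1. **Is the restriction stated, or only inferred from silence?** It is stated, as a rule in Trial monitoring and as an expectation in Emergency code-breaking procedure. Both attach the same causation exception.

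2. **Does the general recording sentence override it?** The window sentence covers AEs and SAEs that are relevant. The paragraph that follows says which kinds of event are not reported as AEs or SAEs. Read in order, the specific rule narrows the general one.

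3. **Does the fallback put the excluded events back?** The fallback promises recording in line with normal practice, and it is set against reporting as AEs or SAEs. It does not say where that record sits or how it would reach the trial's AE data. The text does not clearly restore these events.

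4. **Who applies the condition?** Trial monitoring has participants raise AEs with clinic staff or the trial team. Consent and assent makes the primary care dentist the principal investigator, and Trial management and oversight arrangements makes that investigator responsible for checking the CRFs. The Blinding section says staff cannot be blinded. On this route the judgment is made with knowledge of the arm. Trial monitoring also already describes the tested arm as the less invasive one, so expectation could influence attribution.

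5. **Which events are exposed?** Table 2 lists recognized consequences of extraction, local anesthesia, inhalation sedation and general anesthesia. Socket infection, bleeding or a reaction to an anesthetic agent would probably be reported under any reading. What remains exposed is the admission, medication change or other problem whose cause is uncertain.

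6. **What does the intervention mean in the rule?** Interventions uses the word for the arm without the compensating extraction. Participant recruitment and retention uses it for the one-tooth versus two-tooth comparison, and Table 2 includes the anesthetics. The broad meaning is the better reading, but the rule does not say so. This is a secondary wording point.

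7. **Which outcomes are touched?** Primary outcomes, Secondary outcomes and the comparisons under Data management and statistical methods do not include AEs. Type of anesthetic is a secondary outcome, but it is collected on the CRF without a causality condition.

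**The case against.** The strongest reply is that the article separates reporting from recording. On that view the condition only limits what is passed on, while everything is still written down. The wording allows this reading, and the code-breaking section is softer than the monitoring section. But the restriction covers reporting as AEs as well as SAEs, so it is hard to read as a limit on expedited reporting alone. If that was the intention, the text needs to say so.

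A second reply is that the standard operating procedure governs and may define causality categories. It is not shown, and it may. The article's own exclusion still stands beside it, and a site following the article as written would apply it.

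A third is that the procedure is routine and low risk, the window is short, and no between-arm AE comparison is listed. All of this stands, and it sets the severity.

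A reader might infer more than the documents support:

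- **That AE data will be biased by arm.** Knowledge of allocation makes unequal reporting possible, but nothing shows its size or direction.
- **That the plan is at fault for naming no blinded causality assessor.** A condensed article may leave that to the procedure or the full protocol, and the fix below would not supply one.
- **That excluded events cannot be recovered.** Consent and assent says parents "must agree to researchers and regulatory representatives having access to their medical records for monitoring and audit purposes", but it does not say that this is the sole permitted use. Trial management and oversight arrangements also provides for site monitoring and for access to source documents at audit.

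One practical objection also holds. Capturing every medication change would bring in ordinary pain relief after extraction, since Table 2 lists pain and swelling as common. The fix therefore exempts it.

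**Conclusion.** The point holds as a minor one about safety reporting. Two sections make direct evidence of causation a condition for treating hospital admissions, medication changes and other health problems as AEs or SAEs, and staff who know the allocation are placed to apply it. Acute events of uncertain cause after an extraction or anesthetic can therefore be left out of the trial's AE data. With no independent data monitoring committee, completeness of those data matters somewhat more.

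The effect on bias cannot be quantified. No listed primary or secondary outcome, sample size figure or planned between-group comparison changes. The conclusion assumes that sites follow the article as written and that the standard operating procedure does not override the exclusion. If the procedure already requires capture regardless of cause, what remains is a contradiction in wording to remove.

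**What to change.** Replace the causation condition in Trial monitoring and in Emergency code-breaking procedure, keeping the present window from consent to day 10:

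- **Capture.** In both arms, record all unplanned hospital admissions, other serious events, and new prescribed medication or unplanned treatment, whatever the attributed cause.
- **Exempt.** Leave out planned admission for the anesthetic and routine pain relief after extraction.
- **Grade separately.** Add one CRF field asking whether the event was related to any extraction or anesthetic given at the trial treatment session. Include a possibly-related category in place of the direct-evidence threshold. This wording also covers a child who has both lower first molars removed at one session, and it settles what the intervention means.
- **Tabulate.** Show events by allocated arm without filtering on causality, with relatedness alongside.

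Relatedness would still be judged by people who know the arm, but it would no longer decide whether an event enters the data. The cost is a wording change in two sections, one CRF field and some extra entries for unrelated background events. No new visit or procedure is needed.

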#### Trial management and oversight arrangements

The cosponsors of this trial are the University of Dundee and NHS Tayside.

The trial will be coordinated by the Trial Management Group, (TMG) consisting of the chief investigators, investigators, representative(s) of site PIs, TCTU senior clinical trial manager and a statistician. This group will meet regularly throughout the trial.

A TCTU trial manager will oversee and coordinate the study and will be accountable to the chief investigator. The PI at each site will be responsible for checking the CRFs for completeness, plausibility and consistency. Any queries will be resolved by the investigator or delegated member of the trial team.

A delegation log will be prepared for each site, detailing the responsibilities of each member of staff working on the trial.

The Central Trials Office, TCTU, will provide support to the study team. The office will be responsible for randomization, collection of data in collaboration with the trial manager, data processing and analysis. Publication and dissemination of the study results will be coordinated by the chief investigators and the TCTU, who have had an advisory role in this trial.

A Trial Steering Committee has been established to oversee the conduct and progress of the trial. This comprises: the co-chief investigators, co-investigators, a representative from Tayside Medical Sciences Centre, a practitioner representative and a patient representative.

An independent Data Monitoring Committee will not be necessary for this trial as the study is low risk.

Principal investigators and institutions involved in the study will permit trial-related monitoring, audits, Research Ethics Committee (REC) review, and regulatory inspection(s). In the event of an audit, the investigator agrees to allow the sponsor, representatives of the sponsor or regulatory authorities direct access to all study records and source documentation.

This study has been reviewed by the University of Dundee sponsorship review and is considered low risk, however to ensure the study is run to GCP standards the site will be regularly monitored by the Co-Chief Investigator, [name], or a representative of TASC as agreed by the sponsor.

#### Investigator responsibilities

The principal investigators are responsible for the overall conduct of the study at their site and compliance with the protocol and any protocol amendments. In accordance with the principles of GCP, the following areas listed in this section are also the responsibility of the investigator. Responsibilities may be delegated to an appropriate member of study site staff, which in this case are senior clinical dental staff who have been nominated as co-investigators. Delegated tasks must be documented on a delegation log and signed by all those named on the list.

#### Emergency code-breaking procedure

Emergency code-breaking in this randomized control trial is not applicable because the pattern of tooth extraction is visible.

The proposed intervention is unlikely to result in SAEs or SuSARS. We do not expect to report hospital admissions, changes in concomitant medications or other health problems as AEs or SAEs unless there is direct evidence that the AE has been caused by the intervention. However, should they occur, they will be recorded in keeping with normal practice.

### Ethical consideration

#### Research ethics approval

The study will be conducted in accordance with the principles of GCP. Approval will be obtained from the appropriate REC and local National Health Service Research and Development (R&D) approval will be obtained prior to commencement of the study at any site.

#### Protocol amendments

Any changes in research activity, except those necessary to remove an apparent, immediate hazard to the participant, will be reviewed and approved by one of the co-chief investigators. Amendments to the protocol will be submitted in writing to the appropriate REC and local R&D for approval prior to participants being enrolled into an amended protocol.

In the event that an investigator needed to deviate from the protocol, the nature of and reasons for the deviation will be recorded in the CRF. If this necessitates a subsequent protocol amendment, this will be submitted to the REC and local R&D for review and approval if appropriate.

#### Consent and assent

Where patients attend their own primary care dentist, these dentists will act as principal investigators and will obtain consent from the patients. Patients attending the Dundee Dental Hospital and receiving treatment there will give consent to one of the trial team wherever possible. If this is not possible, a suitably trained dentist will obtain consent. Regardless of location, consent of the patients will be performed by dentists who will be conversant with the study design and protocol, and be GCP trained in line with the Research Governance Framework (RGF).

The parent(s)/legal guardian(s) of all children in the study will provide written informed consent before any study procedures are carried out and a participant information sheet will be provided to facilitate this process. Where possible, and with the agreement of the parent(s)/legal guardian(s), participating children will also be asked to provide written or oral assent. Those not competent in English will be invited to bring an interpreter with them to the subsequent treatment appointment or to request an NHS interpreter, where this service is available.

As part of the consent process parent(s)/legal guardian(s) must agree to researchers and regulatory representatives having access to their medical records for monitoring and audit purposes. Parent(s)/legal guardian(s) may withdraw their consent to participate at any time during the study.

The investigator or delegated member of the trial team and the child should sign and date the Assent form whereas the parent and investigator should sign the Informed Consent form(s) to confirm that consent has been obtained. The participant should then receive a copy of this document and a copy should be filed in the investigator site file (ISF).

#### Withdrawal procedures

Parent(s)/legal guardian(s) will be informed that they have the right to withdraw their child from the study at any time. The right to refuse to participate without reasons will be respected. After the participant has entered the study the clinician remains free to give alternative treatment to that specified in the protocol at any stage if he/she feels that it is in the participant’s best interest, but reasons for doing so will be recorded. In these cases the participants remain within the study for the purposes of follow-up and data analysis. All participants will be free to withdraw at any time from the study without giving reasons and without prejudicing further treatment.

Due to the extended follow-up period for this trial (5 years), some children may be lost to follow-up. If a patient withdraws due to geographical reasons or because he or she is receiving treatment elsewhere, it may be feasible to send the review questionnaire to that patient, as we will attempt to track all patients using their CHI number by contacting their GP or GDP. Attempts will be made to continue data collection from the patient through the new GDP.

If the level of withdrawn participants is high it may be necessary to extend the recruitment period.

For participants who withdraw and do not wish to receive study related interventions, then no further contact will be made by the study team.

The study team can not foresee any incidences where a participant would be withdrawn for safety reasons as this is considered to be a one-off low risk intervention and involves routine dental practice of a common procedure (that is, dental extraction).

